### Data management

Case report forms (CRFs) and all measurement data (with the exception of the spasticity and contracture measurement data) will be completed on paper forms. Data will then be entered and stored in a password protected electronic database. The original paper copies of CRFs and all study data will be treated as confidential documents and held securely in accordance with regulations. Participants will each be assigned a unique trial identity code for use on all study documents. All source documents will be filed at the principal investigator's site.

### Data analysis

Data will be statistically summarised/analysed using SPSS, and MathCad will be used to extract measures related to spasticity and contractures. Analyses will cover the following:
Total patients recruited within 72 h of stroke event; average length of time post-stroke when patients received first treatment.Total patients screened, eligible and approached, consented, and excluded after screening.Total patients who completed the intervention; number who completed 3-month, 6-month and 12-month follow-up assessments.Total participants receiving ES per protocol (PP); mean, minimum and maximum number of ES treatments received during 3-month intervention period; qualitative patient/carer interview data, and ES machine's memory which records number of sessions and duration.Total patients unable to give informed consent; number consented by consultee; number of consultees who declined.Recruitment and attrition rates, number of patients lost to follow-up and reasons.Quality of health economic data between assessment points especially 6–12 months regarding completeness. Cross referencing of data against medical records where possible. Sensitivity of the EQ-5D in measuring outcome. Combined cost and outcome analysis to determine potential cost-effectiveness of ES verses usual care.Thematic analysis will be used to identify themes representative of patient experience of treatment, and the experience of carers with the application of the ES device.

As the sample size is small and a method of minimisation is used, we propose to estimate effect size (using the Cohen's d and the 95% CI) for the main study measures that are interval level data. The OR (and the 95% CI) will be estimated when data are dichotomous. When measures are ordinal, nominal relative risk ratios will be used to present all forms of adverse events.

In addition to estimating effect size, we will explore the use of the following statistical techniques to analyse our data: The group of patients randomised to receive the active treatment will be compared with the control group for all our primary outcomes variables recorded. Continuous variables that are normally distributed will be analysed using generalised linear modelling techniques. Where repeated measures have been recorded, we will apply generalised estimating equation techniques, considering appropriate correlation structure, with time interaction. For continuous variables, treatment differences will be presented with associated 95% CIs. For all statistical tests p<0.05 (2-sided) will be considered statistically significant.

No additional secondary analyses (eg, subgroup or adjusted analyses) are planned for this feasibility study.

For this study, the following definitions of analysis population will be followed:

*All-available-patient population*: All patients who have consented for the study will be used for patient accountability and listings and will include patients who are randomised but who do not receive their ES intervention treatment.

*Intention-to-treat (ITT) population*: All patients who have been randomised and received their ES treatment intervention at baseline and who complete follow-up assessment at 3 months, 6 months and 12 months will be included in an ITT population.

*The PP population*: All patients included in the ITT population, who participate in the study, without major protocol violation.

Missing values will be imputed by using the last value carried forward. We acknowledge that this method is associated with a risk of bias in patients who are deteriorating.

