## Methods and analysis

### Study objectives

The primary objective of the study is to evaluate the feasibility of a RCT that will test the efficacy of delivering early, intensive ES to prevent poststroke complications (such as pain and contractures) to the paretic (weak) upper limb after stroke.

The objectives of this feasibility study therefore are to determine whether:
It is feasible to recruit within 72 h after stroke event, and to ascertain recruitment rates.Initiating ES therapy within 72 h after stroke event is appropriate.The ES regime proposed, that is, to start receiving ES on an acute stroke unit twice a day, 5 days a week and to continue with this schedule postdischarge for up to 3 months in total, is feasible, as measured by compliance, attrition and the qualitative work.Study the interaction between compliance and response to treatment in order to identify the optimum compliance.To determine preliminary health economic information surrounding the costs and benefits of the intervention.

We will also determine in this feasibility study what the most appropriate inclusion/exclusion criteria are; what the most sensitive and acceptable outcome measures are; the optimum method for single blinding and any barriers to compliance to the protocol from both the therapist and patient perspectives.

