### Randomisation

Following baseline measures, participants will be randomised to ES therapy intervention or usual care control. All participants eligible for inclusion will be randomised on a 1:1 basis. Concealed random allocation will be conducted by a statistician using a computer-generated pseudo-random list with random permuted blocks of varying sizes. Allocation concealment will be ensured by the statistician preparing the randomisation codes in sealed envelopes that will only be opened by the researcher after the patient has been recruited and has completed all baseline measurements. Participants will be stratified into four groups (n=10):
No arm movement (Action Research Arm Test (ARAT)^21^ score=0) and cognitive impairment (Montreal Cognitive Assessment (MoCA)^22^ <26);No arm movement (ARAT^21^ score=0) but no cognitive impairment (MoCA^22^
>26);Some arm movement (ARAT^21^ score >1) and cognitive impairment (MoCA^22^ <26);Some arm movement (ARAT^21^ score >1) but no cognitive impairment (MoCA^22^
>26).

A minimisation technique will be applied during randomisation with minimisation on: age, sex, side of stroke and severity of arm weakness (as measured by the NIHSS^20^ arm subscore).

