### Outcome measures

The primary outcomes relate to the feasibility outcomes of the study.
Feasibility of the trial design:
Recruitment rates: number/per cent of participants recruited within 72 h post-stroke; time post-stroke that participants received their first treatment;Recruitment strategy: number/per cent of patients screened, number/per cent eligible and approached, number/per cent who consented, number/per cent excluded after screening;Completion/attrition rates: number/per cent of participants who completed the intervention;Compliance/adherence to treatment protocol: number/per cent of participants who received ES twice a day, 5 days a week while in hospital, and number/per cent who continued with the treatment regime after discharge. Mean, minimum and maximum number of ES treatments that participants received during the 3-month intervention period;Consultee consent rates: number/per cent of patients unable to give informed consent, and number/per cent consented by a consultee, number of consultees who declined consent;Tolerability: number of participants who withdraw or decline intervention; records of interventions declined and why;Integrity of the study protocol: measured by examining how many participants are able to complete the study, number/per cent of missing data, and number/per cent of people who completed each of the outcome measures at 3-month, 6-month and 12-month follow-up, calculation of the cost of running the study; analysis of the qualitative interview and focus group data. The secondary outcomes relate to clinical outcome measures. Demographic characteristics (age, gender, ethnicity and socioeconomic status), stroke characteristics (date, type and side of stroke), cognitive status (MoCA^22^) and premorbid function state (Nottingham Extended ADL (NEADL)^24^) will be collected at baseline.

Participants will complete the following assessments at 0, 3, 6 and 12 months:
Neurological outcome (NIHSS^20^ score);Independence in daily activities (Barthel ADL Index score^25^ and modified Rankin Scale (mRS)^26^
^27^);Pain in the affected arm (Scale of Pain Intensity (SPIN)^28^);Muscle contractures/muscle activity (Biometrics EMG equipment);Arm function (ARAT^21^);Stroke-related quality of life (Stroke Specific Quality of Life Scale (SS-QOL))^29^;Health status (EuroQol-5D (EQ-5D)^30^);Patient resource use questionnaire;Carer strain (Caregiver Strain Index (CSI)^31^) will be completed by the participant's nominated carer.

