### Sample size

This is a feasibility study and therefore the sample size is determined by the number of participants that is feasible to study within the timescale of the project. Consecutive sampling will be used to recruit 40 participants. This will provide sufficient information to indicate feasibility. Outcome data will be utilised to inform a sample size calculation for the definitive trial by assessing variability and completeness of data.

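### No adjusted analyses are planned, although allocation is balanced on likely prognostic factors and the clinical scales are measured at baseline; if those factors predict outcome, the 95% CIs for continuous secondary outcomes are too wide

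*Protocol article*

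**What the plan says.** The Randomisation section balances the arms in two ways. First, "Participants will be stratified into four groups (n=10", the groups being defined by arm movement (ARAT) crossed with cognitive impairment (MoCA). Second, "A minimisation technique will be applied during randomisation with minimisation on: age, sex, side of stroke and severity of arm weakness", with weakness measured by the NIHSS arm subscore.

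Under Outcome measures the clinical scales are secondary: "Participants will complete the following assessments at 0, 3, 6 and 12 months". They include NIHSS, Barthel, mRS, SPIN, contracture measures, ARAT, SS-QOL and EQ-5D.

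The Data analysis section introduces effect estimation with the words "As the sample size is small and a method of minimisation is used". It proposes Cohen's d with a 95% CI for interval measures and an OR for dichotomous ones. It then says that generalised linear models, and GEE with a time interaction, will be explored. It names no covariate and closes the subject: "No additional secondary analyses (eg, subgroup or adjusted analyses) are planned for this feasibility study".

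The Sample size section says that outcome variability from this trial will inform the sample size of the definitive trial.

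**The concern.** Balancing the arms on a prognostic factor removes that factor's contribution from the true sampling variance of the treatment difference. An unadjusted standard error still counts it as noise, so the interval is wider than its nominal level requires. The month-0 value of each scale, already collected, is also left unused in Cohen's d.

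The factors are likely to be prognostic. ARAT defines two of the four strata's boundaries and is itself an outcome. The NIHSS arm subscore is a minimisation factor, and the NIHSS score is an outcome.

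Two things are at stake. With 40 participants the intervals are already wide, and precision is given away. Also, a definitive trial analysed with baseline adjustment should be sized on the residual SD, or on the total SD with the baseline correlation, and the plan does not commit to reporting either pair. This is a stated choice in the article, not a detail left to an analysis plan that is not shown.

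**Working it through.** There is no planned figure to reproduce. The total of 40 (Sample size section) is pragmatic, with no effect size, SD or power. The only arithmetic in the text, 4 strata × 10 = 40, is consistent.

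**Inputs from the protocol:** N = 40; 1:1 allocation, so about 20 per arm; two-sided 5% level; two stratifiers and four minimisation factors. **Assumed, because the protocol gives neither:** R² between the balancing factors and the outcome, and r between baseline and follow-up.

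**1. Unadjusted precision.** Half-width in SD units = t(0.975, 38) × √(2/20) = 2.024 × 0.316 = 0.64.

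**2. Coverage under minimisation.** Simulation with N = 40, no treatment effect, biased-coin minimisation (probability 0.8) on all six factors, with the stratifiers treated as minimisation factors; 4,000 runs per row. Simulation error near 95% is √(0.95 × 0.05 / 4000), about 0.3 percentage points. The adjusted model includes all six factors.

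| Assumed R² | Coverage, unadjusted | Coverage, adjusted | Half-width, unadjusted | Half-width, adjusted | Change in width |
|---|---|---|---|---|---|
| 0 | 94.5% | 94.8% | 0.636 | 0.658 | +3% |
| 0.09 | 95.9% | 95.3% | 0.636 | 0.627 | −1% |
| 0.25 | 97.2% | 95.7% | 0.637 | 0.570 | −11% |
| 0.36 | 97.2% | 94.9% | 0.639 | 0.527 | −18% |
| 0.50 | 98.3% | 95.4% | 0.640 | 0.466 | −27% |

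**3. Upper case: four strata of 10, each split exactly 5:5.** The true standard error is then about √(1 − R²) times the one reported, so coverage is roughly P(|Z| < 1.96/√(1 − R²)):
- R² = 0.25: 1.96/0.866 = 2.26, coverage 97.6%
- R² = 0.40: 1.96/0.775 = 2.53, coverage 98.9%
- R² = 0.50: 1.96/0.707 = 2.77, coverage 99.4%

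Repeated simulation of this case agrees to within a few tenths of a point, with a highest value of 99.5%.

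**4. Adjusting for the baseline value alone.** Half-width = t(0.975, 37) × √(2/20) × √(1 − r²). This gives 0.61 at r = 0.3, 0.55 at r = 0.5, 0.46 at r = 0.7 and 0.38 at r = 0.8, against 0.64 unadjusted. Ignoring the degree of freedom, 40/(1 − r²) expresses the gain as patients: 44 at r = 0.3, 53 at r = 0.5, 78 at r = 0.7.

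**5. Effect on the definitive trial.** If that trial is analysed with baseline adjustment but sized on the total SD, the calculated sample is too large by 1/(1 − r²). At r = 0.5 this is 1/0.75 = 1.33, or one third.

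**The case against.** The case for leaving the plan alone has force. "The primary outcomes relate to the feasibility outcomes of the study"; these are counts and rates with no baseline value, so adjustment is irrelevant to them. The trial is not powered for efficacy, the models are only to be explored, and over-coverage does not inflate false positives. A simple analysis of 40 patients is defensible. All of this stands. It limits the weight of the point but does not remove it, because the plan still commits to effect sizes, 95% CIs and tests at p<0.05, and uses the variability to plan the next trial.

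The magnitude is also open to challenge. "Consecutive sampling will be used to recruit 40 participants", so equal strata with exact 5:5 splits are not guaranteed and the 99.5% figure is a favourable extreme. The gain will differ by scale: contracture measures taken soon after stroke, with fixed contractures excluded (Table 1), may predict little. That stands too.

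Several stronger readings are tempting and are not supported:
- A reader might infer that minimisation is offered as the reason for leaving effects unadjusted. The sentence gives small size and minimisation as reasons to estimate effect sizes; it does not mention adjustment.
- A reader might infer that the baseline correlation and residual SD can never be obtained. The GEE could treat month 0 as a response and recover part of this information. The text does not say whether it will. Cohen's d, the OR and the absence of allocation factors are unaffected by that possibility.
- A reader might infer that the sentence contradicts the objective "Study the interaction between compliance and response to treatment in order to identify the optimum compliance". It excludes additional secondary analyses and names subgroup and adjusted ones as examples. An analysis serving a stated objective is not plainly additional, and its method may sit in a plan not shown.

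**Conclusion.** The point holds for the continuous secondary clinical outcomes. Planning no adjustment after balancing on likely prognostic factors gives 95% CIs that are too wide: true coverage of about 97% to 98% under minimisation, and up to about 99.5% under exact 5:5 strata, for R² between 0.25 and 0.50. The direction is certain if the factors are prognostic. The size rests on assumed values of R² and r. At R² = 0.09 the gain is negligible, and at R² = 0 adjusting for all six factors makes the interval about 3% wider.

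The consequence is moderate: lost precision, and a missed chance to report the quantities on which an adjusted definitive trial would be sized. The feasibility conclusions are unaffected.

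A separate, minor point concerns the compliance objective. Compliance with ES exists only in the ES arm, about 20 participants, and arises after randomisation, so severity and recovery may plausibly drive it. An optimum cannot be identified from it. For scale, an assumed observed correlation of 0.30 in 20 participants has a Fisher-z 95% CI of −0.16 to 0.66.

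**What to change.** In the Data analysis section, replace the sentence ruling out adjusted analyses with text to this effect:

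- Each continuous secondary clinical outcome will be estimated as a mean difference with 95% CI, adjusted for its own month-0 value and a small set of allocation factors, the ARAT and MoCA strata at least.
- Cohen's d will stay standardised by the total (pooled) SD. Dividing by the residual SD would make d grow with R² and lose comparability across studies.
- Total SD, residual SD and baseline/follow-up correlation will be reported for each scale, so that the definitive trial can be sized on the analysis it will use.
- Where an OR is adjusted, the report will state that adjustment changes the estimand.

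The statement that no subgroup analyses are planned can remain.

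Separately, reword the compliance objective as an exploratory description of adherence and its association with outcome, without inferring an optimum.

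Cost: wording, a few degrees of freedom, and slightly wider intervals if the factors explain almost nothing. The covariate set should stay small at N = 40. No new data are needed.

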### Intervention treatment

Treatment with current controlled ES is delivered using a two channel constant current stimulation (maximum output 100 mA, pulse width 450 μs and a frequency between 40 and 60 Hz as per participant preference)^i^. The motor points for stimulation are selected to produce reciprocal flexion and extension through full range of movement.^23^ The initial assessment and treatment session with an NHS band 5 or above physiotherapist or occupational therapist will involve identification of the motor points for the forearm flexors and extensors, and placement of self-adhesive electrodes over these motor points. The current intensity will be increased to produce an alternating contraction of the flexors and extensors using a flex-hold-extend-hold pattern, ensuring that a pure movement is produced with no ulnar or radial deviation. The skin will be marked with a skin-safe marker pen to show the correct area to place the electrodes for future treatments and the ES device will be locked to the selected settings. A single stimulation and hold cycle will last 20 s and this will be cyclically repeated for 30 min after which the device can be removed.

Clinical staff will assist the patient to apply the electrode pads to the premarked motor points and switch on the device to the prestored treatment setting (this will take between 2 and 5 min) for subsequent treatments. The device will provide treatment without the need for a therapist to be present.

Prior to hospital discharge, the patient and/or nominated carer will be taught how to self-manage the treatment where possible. Treatment will continue twice a day, 5 days a week (Monday to Friday), for a total period of 3 months.

Modifications will not be made to the intervention. A participant may discontinue their allocated intervention or withdraw from the study for the following reasons: withdrawal of consent, or changes to their health status preventing their continued participation. Whenever possible, study participants will be retained in the trial to enable follow-up data collection and prevent missing data.

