### Usual care control

Participants randomised to the control group will not receive ES therapy but will receive all usual care. ‘Usual care’ will include all the therapy interventions that are standard practice on the Nottingham Stroke Unit. As per national clinical guidelines,^2^ the application of ES to the upper limb is not standard practice. It is not possible to provide a placebo device without the possibility of it being easily identified as such. One reason is because movement is seen in the upper limb when the ES device is activated; furthermore, participants will be recruited and start treatment while on the hospital ward, so control and intervention participants may be in close proximity on the same wards as each other and would likely notice a difference between the intervention and placebo devices.

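### The population labelled ITT requires receipt of ES and attendance at every follow-up, so no stated analysis population keeps all randomised participants as allocated

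*Protocol article*

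**What the plan says.** All three populations are defined in the protocol article under Data analysis.

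- **ITT.** Membership goes to "All patients who have been randomised and received their ES treatment intervention at baseline and who complete follow-up assessment at 3 months". The sentence continues so that only those who "complete follow-up assessment at 3 months, 6 months and 12 months will be included in an ITT population". The visits are joined by *and*, so all three are required.
- **Per protocol.** "All patients included in the ITT population, who participate in the study, without major protocol violation". This is a subset of the ITT set.
- **All-available-patient.** Defined by consent rather than randomisation, this set "will be used for patient accountability and listings and will include patients who are randomised but who do not receive their ES intervention treatment".

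The same section states the intended contrast: "The group of patients randomised to receive the active treatment will be compared with the control group". It also says that missing values will be imputed by carrying the last value forward. Under Usual care control: "Participants randomised to the control group will not receive ES therapy but will receive all usual care". Study design describes a two-arm 1:1 superiority trial. Sample size gives 40 participants and says that outcome data will inform the definitive trial's sample size through variability and completeness.

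**The concern.** An intention-to-treat set should depend only on randomisation. This one depends on two later events: receiving ES and attending three assessments over 12 months. The first can exclude people from one arm only. The second can exclude people from both, and probably not at random, since death, withdrawal and missed visits after stroke tend to follow severity.

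The plan intends to report Cohen's d and odds ratios with 95% CIs, to explore generalised linear and GEE models, and to use outcome variability to plan the definitive trial. If these come from the set as defined, they describe participants who started treatment and stayed to the end, under a label that tells readers the opposite. There is also an internal conflict with the imputation rule.

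**Working it through.** The plan states no power, effect size, SD, non-start rate or drop-out rate, so there is no figure of its own to reproduce. The check applies the definition to the design.

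**1. Literal reading.** 40 participants at 1:1 gives 20 per arm. Controls receive no ES, so the set holds at most 20 ES participants and 0 controls. No contrast between arms can be estimated.

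**2. Probable intended reading.** Suppose *their ES treatment* means *their allocated treatment*. A control then qualifies by completing all visits; an ES participant must also have started ES. Let s be the share of the ES arm that starts and c the share completing all visits (the same in both arms, and independent of starting). Then n(ES) = 20·s·c and n(control) = 20·c. Both rates are assumptions: s = 0.8 to 1.0, c = 0.6 to 0.9.

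| s | c | ES n | Control n | Total of 40 | 95% CI half-width for d near 0 |
|---|---|---|---|---|---|
| 1.0 | 0.9 | 18.0 | 18.0 | 36.0 | 0.65 |
| 0.9 | 0.9 | 16.2 | 18.0 | 34.2 | 0.67 |
| 0.8 | 0.8 | 12.8 | 16.0 | 28.8 | 0.74 |
| 0.8 | 0.6 | 9.6 | 12.0 | 21.6 | 0.85 |

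The half-width is 1.96·√(1/n1 + 1/n2). With 20 per arm it is 0.62.

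**3. Spurious effect when ES does nothing.** Let the outcome be standard normal, and let exclusion act on the lower tail of a latent variable correlated ρ with it. Removing a fraction p raises the mean by ρ·φ(z_p)/(1−p), in units of the unselected SD. The excluded fractions are 1−s·c in the ES arm and 1−c in controls. The spurious d is the difference between the two shifts.

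| s | c | Excluded ES / control | φ(z)/(1−p) ES / control | d at ρ=0.3 | d at ρ=0.5 |
|---|---|---|---|---|---|
| 0.9 | 0.9 | 0.19 / 0.10 | 0.335 / 0.195 | 0.042 | 0.070 |
| 0.8 | 0.8 | 0.36 / 0.20 | 0.585 / 0.350 | 0.070 | 0.117 |
| 0.8 | 0.6 | 0.52 / 0.40 | 0.830 / 0.644 | 0.056 | 0.093 |

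A simulation of these three scenarios gave the same values. Other pairings with s = 0.8 or 0.9 widen the range slightly: 0.027 at s = 0.9, c = 0.6, ρ = 0.3 (0.3 × (0.735 − 0.644)), and 0.136 at s = 0.8, c = 0.9, ρ = 0.5 (0.5 × (0.468 − 0.195)). At s = 1.0 the excluded fractions are equal and the shift is zero.

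**4. Is there another population to use?** Per protocol is a subset, so it inherits every exclusion. The all-available set does include untreated randomised patients, but its stated purpose is that it "will be used for patient accountability and listings". No stated set is all randomised participants as allocated, for use in estimating effects.

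**5. Consistency with the missing-data rule.** A participant who misses an assessment is already outside the set, so no missed visit is left to carry a value into. At most the rule could fill single measures missing within an attended visit.

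**The case against.** The strongest defence is that this is a feasibility trial. Primary outcomes are feasibility measures, clinical outcomes are secondary, the modelling is exploratory, and 40 was not chosen for power. A bias of 0.04-0.12 is small beside a CI half-width of at least 0.62. All of this stands and limits the consequence, but it does not make the definition right.

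Four stronger readings are tempting, and the document does not support them.

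- *Controls will be left out.* The announced comparison and the two-arm design show that they were meant to be included. The empty control arm is a wording fault, not a forecast.
- *The definition defeats the retention policy and selects adherers.* Under Intervention treatment, wherever possible "study participants will be retained in the trial to enable follow-up data collection and prevent missing data". ES is required only at baseline, so someone who stops ES later but attends every visit stays in the set. The policy is undercut only for those who never start or who miss an assessment.
- *Attrition will be understated.* Outcome measures and Data analysis plan separate counts of completion at each follow-up, losses with reasons, and missing data. Nothing assigns these to the ITT set.
- *A null effect could shift by 0.27 to 0.42 SD.* That needs 15-25% of the ES arm excluded, no controls excluded, and exclusion perfectly ordered by prognosis. On the intended reading visit completion applies to both arms, and only failure to start ES is one-sided.

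Nor does the Sample size section name the observed effect as an input to the definitive trial. The direct route is through outcome variability, and the loss there has not been quantified.

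**Conclusion.** The definition is wrong as written and should be corrected before analysis. Taken literally, it makes the planned comparison impossible; taken as intended, it conditions on events after randomisation while carrying the ITT label. No other stated population fills the gap, and the completion condition leaves the imputation rule without missed visits to act on.

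The size is uncertain because the document gives no rates. On the assumed 80-100% starting and 60-90% completing, about 22 to 36 of 40 remain. The spurious d in favour of ES is about 0.04-0.12 in the three scenarios worked (80-90% starting, correlation 0.3-0.5) and about 0.03-0.14 over all pairings with 80 or 90% starting. It falls to zero if everyone starts and drop-out acts equally in both arms. The defect in the definition does not depend on these assumptions; only its size does.

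**What to change.** Replace the ITT paragraph with: all randomised participants, analysed in the group to which they were allocated, irrespective of ES received or follow-up visits completed, using every available assessment. In the same edit:

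- State that effect sizes, CIs and outcome variability come from this set.
- Reconcile it with the missing-data rule. For example, let the planned repeated-measures model use all observed visits, with last value carried forward at most as a sensitivity analysis. An unweighted GEE on observed data assumes that data are missing completely at random, and the text should say so.
- Relabel the current set treated completers and keep it only as a sensitivity analysis.
- Define the per-protocol set separately for each arm, with no ES-receipt condition for controls.

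The cost is about one paragraph of protocol or SAP wording. It needs no extra patients or data collection and no change to treatment.

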### Participants

The study is set in Nottingham, England. Participants will be patients recruited from the Stroke Unit of the Nottingham University Hospitals NHS Foundation Trust within 72 h of stroke event.

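### Carrying the last value forward from an acute baseline can distort the effect size and SD meant for the definitive trial, has no rule for death, and conflicts with the completer-only ITT set

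*Protocol article*

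**What the plan says.** All of this is in the protocol article.

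- **Missing-data rule (Data analysis).** "Missing values will be imputed by using the last value carried forward". The sentence is not limited by outcome, visit, reason or population. The caveat that follows is "We acknowledge that this method is associated with a risk of bias in patients who are deteriorating". Nothing is said about patients who improve or who die.
- **Timing.** Participants says "Participants will be patients recruited from the Stroke Unit of the Nottingham University Hospitals NHS Foundation Trust within 72 h of stroke event". Data collection methods places the baseline measurements on the ward after recruitment. Outcome measures says "Participants will complete the following assessments at 0, 3, 6 and 12 months", so baseline is the only value that precedes 3 months.
- **Analysis sets (Data analysis).** The ITT set is limited to participants "who complete follow-up assessment at 3 months, 6 months and 12 months will be included in an ITT population". The per-protocol set is a subset of it. The all-available-patient set "will be used for patient accountability and listings and will include patients who are randomised but who do not receive their ES intervention treatment".
- **Model (Data analysis).** For repeated measures, "we will apply generalised estimating equation techniques, considering appropriate correlation structure, with time interaction". Cohen's d with a 95% CI is planned for the main interval-level measures.
- **Use of the results (Sample size).** The outcome data are to inform the definitive trial's sample size "by assessing variability and completeness of data".

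**The concern.** Last value carried forward (LOCF) assumes that a score stays where it was last seen. Here the last value before 3 months is one taken on the ward shortly after the stroke. For a participant lost before 3 months, the acute score would stand in at 3, 6 and 12 months. The caveat covers patients who worsen, but the same rule understates change in those who improve.

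No rule is given for death, so if non-completers are analysed, mRS, Barthel and EQ-5D scores recorded in life could be carried past it.

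The rule also does not fit the ITT definition beside it. A set made up only of people who completed all three follow-ups has no whole missed visit to fill.

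What is at stake is the study's planning output. Cohen's d takes in both the arm difference and the SD, and the observed variability is meant to size the definitive trial. Withdrawals after randomisation are not replaced, and only the ES arm carries a twice-daily regimen for 3 months, so unequal dropout is plausible.

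**Working it through.** The plan has no figure to reproduce: 40 is a feasibility number with no power, SD or dropout behind it. The check therefore asks what LOCF does when baseline is carried to 3 months, over an assumed range.

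**Inputs**
- From the document: 40 participants, 1:1 allocation (20 per arm), two-sided 5% level, visits at 0, 3, 6 and 12 months.
- Assumed, in units of the 3-month SD: R, the mean change from baseline in the control arm (0 to 1.5); d, the true arm difference (0 or 0.5); mT and mC, the shares missing at random in ES and control (10% to 30%); s0, the baseline SD (0.5 or 1). Higher scores are taken as better.

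**Arm difference under LOCF** = (1 - mT)(R + d) - (1 - mC)R.

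With d = 0 this is -(mT - mC)R:

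| Missing, ES v control | R = 0.5 | R = 1.0 | R = 1.5 |
|---|---|---|---|
| equal | 0 | 0 | 0 |
| 20% v 10% | -0.05 | -0.10 | -0.15 |
| 30% v 10% | -0.10 | -0.20 | -0.30 |
| 10% v 20% | +0.05 | +0.10 | +0.15 |

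With d = 0.5 and equal missingness m it is (1 - m) x 0.5, whatever R is: 0.45 at 10% and 0.40 at 20%. With d = 0.5, R = 1 and unequal missingness it can go either way: 0.8 x 1.5 - 0.9 x 1 = 0.30 at 20% v 10%, and 0.9 x 1.5 - 0.8 x 1 = 0.55 at 10% v 20%.

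**Within-arm variance under LOCF** = (1 - m) + m s0² + m(1 - m)(mean change)².
- 20% missing in both arms, d = 0, R = 0.5, s0 = 0.5: 0.80 + 0.05 + 0.04 = 0.89, SD 0.94.
- 20% missing in both arms, d = 0, R = 1.5, s0 = 1: 0.80 + 0.20 + 0.36 = 1.36, SD 1.17.
- Over all combinations the pooled SD runs from about 0.92 to 1.23 times the true value. It falls when baseline scores are bunched and change is small, and rises when change is large.

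**Effect on a later sample size, through the SD alone** (assumed target 0.5 SD and 90% power). N per arm = 2(1.960 + 1.282)² SD² / 0.5², which is 85 at the true SD of 1. With d = 0.5 and 20% missing in both arms, N becomes 80 (R = 0.5, s0 = 0.5), 94 to 106 (R = 1, s0 = 0.5 to 1) or 127 (R = 1.5, s0 = 1).

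**Scale of random error.** The 95% half-width for a difference with 20 per arm is 1.96 x √(2/20) = 0.62 SD.

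**The ITT definition taken literally.** Attrition of 10% to 30% leaves 36 to 28 of 40. None of those has a whole missed visit, and none has died before 12 months. LOCF could then fill only single measures missing at visits that took place.

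**The case against.** The strongest reply is that the protocol's own ITT set disarms the rule. Anyone who died or missed a visit is outside ITT and per-protocol, and the wider set is only for accountability and listings. This stands against any unconditional claim. A reader might infer that scores will be carried past death, or that the arm comparison will be biased, but the text supports only a conditional statement.

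It does not rescue the rule. Read literally, the ITT definition also requires receipt of ES, which Usual care control says that arm does not get, so it cannot be the set actually compared as written. A caveat about patients who worsen suggests that the rule was meant to fill outcomes over time. Even among completers, one measure missed at an attended 3-month visit would take the acute value.

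Other points stand:
- Equal dropout with no true effect gives no bias, and the biases above are smaller than the 0.62 SD half-width.
- The documents give no figure for attrition, death or the size of early recovery.
- For pain and contractures, where worsening is the worry, the caveat fits. The argument about improvement applies mainly to ARAT, NIHSS, Barthel and mRS.
- The primary outcomes are feasibility measures, and the modelling is described as exploratory.

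A reader might also infer that imputation would hide incomplete data. It would not: Outcome measures and Data analysis count missing data, completion of each measure and loss to follow-up directly.

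**Conclusion.** The point holds in conditional form. LOCF is stated as the sole missing-data rule, it is ill-suited to change from an acute baseline, its caveat covers one direction only, and it has no provision for death. It also cannot work alongside the completer-only ITT definition: either it has almost nothing to fill, or it serves a wider set and the ITT definition is wrong.

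If non-completers are analysed, then under the stated assumptions the false difference is 0 to 0.30 SD in size, with a sign that depends on which arm loses more. A true 0.5 SD effect shrinks to 0.45 or 0.40 at 10% or 20% missing in both arms, and the SD is misstated by a factor of about 0.92 to 1.23. It would be tempting to say that the SD is inflated; the calculation shows only that it is distorted. The matter is worth correcting because the SD and effect size are carried forward, not because a decision in this study rests on a p-value.

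**What to change.** In Data analysis:

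1. Drop LOCF as the main rule. For the continuous outcomes, fit a likelihood-based repeated-measures model to the observed visits of all randomised participants, and say that it assumes data missing at random. Ordinal outcomes such as mRS need a method suited to them.
2. Reconcile the ITT definition with this, so that the set compared is all randomised participants and not completers only.
3. Report deaths separately by arm, and state in advance an analysis value where the scale allows one (for example the mRS death category and EQ-5D 0).
4. Compute the SDs and effect sizes to be carried to the definitive trial from observed data.
5. Keep LOCF, if wanted, as a labelled sensitivity analysis, with a caveat that covers improvement as well as deterioration.

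The cost is wording only. No new data are needed, and the model is available in SPSS, which the protocol already names.
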